#### 2.5.2. Secondary Outcomes

Secondary outcomes will include the longitudinal assessment of cardiopulmonary parameters, oral health conditions, smoking-related outcomes, health-related quality of life, oral health-related quality of life, and participants’ adherence, usability, acceptability, and patient and healthcare satisfaction with the rehabilitation program.

Cardiopulmonary parameters will include heart rate (beats per minute, bpm), blood pressure (mmHg), respiratory rate (breaths per minute), and oxygen saturation (SpO_2_, %). Heart rate, blood pressure, respiratory rate, and oxygen saturation will be measured twice daily throughout the 12-month study period. In the EG, these parameters will be automatically recorded twice daily through wearable remote-monitoring devices and transmitted to the integrated telemedicine platform. In the CG, the same parameters will be manually self-recorded twice daily using portable medical devices (sphygmomanometers and pulse oximeters) already available in participants’ possession. In addition, in-person clinical cardiology follow-up evaluations will be performed at baseline, 6 months, and 12 months by cardiology specialists for both EG and CG.Oral health outcomes will include probing depth (PD, mm) [29], full-mouth bleeding index (FMBI, percentage of bleeding sites) [30], and full-mouth plaque index (FMPI, percentage of plaque-positive sites) [31]. These clinical periodontal parameters will be assessed by calibrated dental specialists during standardized in-person periodontal examinations at baseline, 6 months, and 12 months. Periodontal examinations will be performed using a manual UNC-15 periodontal probe, and the periodontal parameters will be measured at six sites per tooth.

In addition, self-reported gingival bleeding during toothbrushing will be self-reported twice daily throughout the study period.

Smoking-related secondary outcomes will include the daily number of cigarettes smoked or equivalent nicotine-containing products used, continuously recorded throughout the study period using the paper-based smoker diary. Nicotine dependence severity will be assessed at baseline, 6 months, and 12 months using the Fagerström Test for Nicotine Dependence (FTND) [32]. Smoking cessation motivation will be evaluated at the same time points using the motivational test developed by the Italian National Institute of Public Health (freely available online on https://smettodifumare.iss.it/documents/d/guest/guida-smetto-di-fumare-a5-v07, accessed on 12 May 2026).Patient-reported outcomes will include health-related quality of life assessed using the Short Form Health Survey (SF-36) [33], oral health-related quality of life assessed using the Oral Health Impact Profile-14 (OHIP-14) [34], and self-perceived periodontal health assessed using the gingival self-assessment questionnaire developed by the Italian Society of Periodontology and Implantology and the European Federation of Periodontology (freely available online on https://www.gengive.org/test-di-autovalutazione-delle-gengive/, accessed on 12 May 2026). All questionnaires will be administered at baseline, 6 months, and 12 months.Technology- and rehabilitation-related outcomes will be assessed at 6 and 12 months and will include usability of the telemedicine platform evaluated through the System Usability Scale (SUS) [35], treatment acceptability and adherence evaluated through the Treatment Acceptability/Adherence Scale (TAAS) [35], and patient satisfaction evaluated through the Client Satisfaction Questionnaire (CSQ-8) [35].Adherence to the rehabilitation program and compliance with wearable device utilization will be assessed at baseline, 6 months, and 12 months. In the EG, adherence to wearable device use will be automatically monitored through the telemedicine platform by recording the timing and frequency of device utilization. In the CG, adherence to the rehabilitation program will be evaluated during scheduled in-person follow-up visits.

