Participants will be randomly distributed equally (in a 1:1 ratio) into the experimental group (EG) and control group (CG). The random allocation sequence will be carried out by the web-based randomization service Research Randomizer (freely accessible online at: https://www.randomizer.org/, accessed on 26 May 2026) by an independent researcher not involved in participant recruitment, eligibility evaluation, or outcome assessment. Allocation concealment will be ensured using sequentially numbered, opaque, sealed envelopes prepared by the independent researcher. The envelopes will be opened sequentially only after the participant has completed the baseline assessment and has been formally enrolled in the study, thereby preventing foreknowledge of treatment allocation and minimizing selection bias.

Due to the nature of the intervention, participants and healthcare providers cannot be blinded to group allocation. Outcome measures will be collected using standardized assessment procedures to minimize assessment bias by independent researchers not involved in participant recruitment, eligibility evaluation, or randomization allocation.

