Specialist-specific contributions are as follows:Cardiologists: optimization of cardiovascular risk factors, therapeutic management, motivational support for smoking cessation, and counseling on the cardiovascular benefits of quitting smoking.Respirologists: assessment and management of respiratory comorbidities, pulmonary function evaluation, support for smoking-related respiratory issues, and counseling on the respiratory benefits of quitting smoking.Dentists: evaluation of oral health, management of smoking-related periodontal disease, and counseling on the oral benefits of quitting smoking.Psychologists: structured behavioral counseling, motivational interviewing techniques, management of psychological dependence, and emotional support.

All sessions are documented in the electronic health record to ensure traceability, reproducibility, and consistency between the two study arms.

On a voluntary basis, participants allocated to the study group will be asked to use the wearable remote-monitoring devices and record physiological parameters twice a day, for a maximum duration of the study of 12 months.

Following enrollment, the EG will receive training on the use of the integrated telemedicine platform and the wearable monitoring devices after the calibration of the devices.

The wearable devices will record participants’ cardiopulmonary parameters (heart rate, blood pressure, respiratory rate, and oxygen saturation) on the integrated telemedicine platform. In this way, the participant’s medical parameters will be automatically recorded through the wearable device and automatically transferred to the telemedicine platform.

Participants will also complete a paper-based smoker diary developed by the Italian Ministry of Health and the National Institute of Public Health (freely available on https://smettodifumare.iss.it/documents/d/guest/guida-smetto-di-fumare-a5-v07, accessed on 12 May 2026), recording the daily number and frequency of cigarettes or nicotine-containing products used.

Adherence to wearable device utilization will be automatically tracked through the telemedicine platform by recording the timing and frequency of device use.

Participants in the EG will also self-report oral health-related parameters, including gingival bleeding during daily oral hygiene procedures performed at least twice a day throughout the rehabilitation program.

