#### 2.3.2. Wearable Remote-Monitoring Devices

The wearable remote-monitoring devices integrated with the BTS TELEREHAB platform are medical-grade, non-invasive tools, including wireless inertial sensors (e.g., G-SENSOR) and pulse oximeters (BTS Bioengineering S.p.A., Garbagnate Milanese, Italy). They collect the following physiological parameters: heart rate, blood pressure, respiratory rate, and peripheral oxygen saturation. Measurements will be collected twice daily for up to 12 months.

Data are acquired by the wearable devices and transmitted in real-time via a secure Bluetooth connection to the patient’s mini-PC Brain unit, which then forwards them to the cloud-based BTS TELEREHAB platform (https://www.btsbioengineering.com/it/products/bts-telerehab/ accessed on 26 May 2026) through an Internet connection (provided there is access to Wi-Fi or a portable hotspot). Data transmission uses encrypted protocols compliant with GDPR.

The system is designed for home and clinical use and has been validated in rehabilitation and telemedicine settings, as described in the BTS TELEREHAB (BTS Bioengineering S.p.A., Garbagnate Milanese, Italy) manuals.

Adherence to device use and data quality will be automatically monitored by the platform.

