### 2.4. Standard Smoking Cessation Program (Control Protocol)

A tailored, multimodal behavioral smoking cessation rehabilitation program delivered exclusively through in-person care will be used for the CG. The behavioral and psychological interventions provided to the CG will be equivalent to those delivered to the EG (described in Section 2.3), differing only in the mode of delivery, namely, face-to-face assistance rather than telemedicine-based rehabilitation.

The behavioral and psychological interventions will be provided during follow-up visits in order to address behavioral difficulties, maintain motivation, and support long-term abstinence.

For home monitoring of cardiopulmonary parameters, portable medical devices already available in participants’ possession, such as sphygmomanometers and pulse oximeters, will be used to manually record heart rate, blood pressure, respiratory rate, and oxygen saturation twice a day for up to 12 months. Unlike the EG, physiological parameters in the CG will not be automatically transmitted to a telemedicine platform, and no wearable remote-monitoring devices will be used. No participant will be required to independently purchase portable medical devices in order to participate in the study, according to the aforementioned exclusion criteria for the CG.

Similar to the EG, participants allocated to the CG will complete a paper-based smoker diary developed by the Italian Ministry of Health and the National Institute of Public Health (freely available on https://smettodifumare.iss.it/documents/d/guest/guida-smetto-di-fumare-a5-v07, accessed on 12 May 2026), recording the daily number and frequency of cigarettes or nicotine-containing products used.

Participants in the CG will also self-report oral health-related parameters, including gingival bleeding during daily oral hygiene procedures performed at least twice a day throughout the rehabilitation program.

Healthcare providers involved in the multidisciplinary smoking cessation program, including dental, cardiologic, pneumological, and psychological specialists, will monitor participants exclusively through scheduled in-person visits according to the rehabilitation program and participants’ clinical needs. Additional in-person specialist evaluations may be scheduled whenever considered clinically necessary.

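### Home cardiopulmonary outcomes are measured by a different system in each arm, so any average device offset can pass for a treatment effect

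*Protocol article*

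**What the plan says.** Section 2.5.2 names four cardiopulmonary secondary outcomes, measured at home twice a day for 12 months. The source depends on the arm.

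- Experimental group (EG): "In the EG, these parameters will be automatically recorded twice daily through wearable remote-monitoring devices". Section 2.3 adds that training follows enrolment and takes place "after the calibration of the devices". Section 2.3.2 describes the equipment as "including wireless inertial sensors (e.g., G-SENSOR) and pulse oximeters".
- Control group (CG): "In the CG, the same parameters will be manually self-recorded twice daily using portable medical devices". Section 2.4 describes these as "portable medical devices already available in participants’ possession, such as sphygmomanometers and pulse oximeters" and adds that "no wearable remote-monitoring devices will be used".

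Both arms also attend the clinic: "in-person clinical cardiology follow-up evaluations will be performed at baseline, 6 months, and 12 months by cardiology specialists for both EG and CG". The text does not say that these visits record the four parameters, or that the between-arm comparison uses them.

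Section 2.6 compares continuous outcomes between arms by t-test or Mann–Whitney test, and models change in primary and secondary outcomes with mixed-effects regression. It mentions no agreement check between devices.

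Section 2.1 makes a general statement: "Outcome measures will be collected using standardized assessment procedures to minimize assessment bias by independent researchers". The Discussion treats control participants' access to devices as a matter of equity and generalizability. It does not list the difference in measurement as a limitation.

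**The concern.** Three things change together with allocation: the instrument, the stated calibration, and the way a reading becomes data (automatic transmission or hand entry). Knowing the arm means knowing the measurement system. If the two systems differ on average, whether through device bias, rounding or recording habits, that difference goes straight into the between-arm contrast. A covariate cannot help, because there is no overlap in device between arms, and neither imputation nor a mixed model creates any.

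At stake is whether a reported cardiopulmonary benefit or harm drawn from home readings could be interpreted. The general assurance in section 2.1 of standardized collection by independent researchers does not fit readings that participants take themselves on assorted personal devices. Section 2.5.2 holds the periodontal outcomes to a stricter standard: calibrated examiners, one type of probe and standardized examinations in both arms.

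**Working it through.** **Step 1. Is confounding complete?**

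| Feature | EG | CG | Section |
|---|---|---|---|
| Device | Study wearable | Participant's own | 2.3.2, 2.4 |
| Calibration stated | Yes | No statement | 2.3 |
| Recording | Automatic | By hand | 2.5.2 |
| Study wearables used | Yes | None | 2.4 |

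No feature overlaps between arms, so confounding is complete.

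**Step 2. Does baseline adjustment remove it?** Section 2.1 has the envelope opened only after the baseline assessment, and section 2.3 places device training after enrolment. The change to the study wearable therefore falls between baseline and follow-up, in one arm only. A change score or a baseline-adjusted model can still carry the offset.

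**Step 3. Reproduce the plan's sample size, to fix n.** Section 2.6 gives one-tailed α = 0.05, power 0.80, a medium effect, and 102 participants (51 per group). Taking medium as d = 0.5 (an assumption; no number is printed):

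- noncentrality = d·√(n/2) = 0.5 × √(51/2) = 2.525, with 100 degrees of freedom
- one-sided critical t = 1.660
- power = 0.806

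With 50 per arm the power is 0.799, so 51 per arm is the smallest adequate n and the stated figure reproduces. It is used below only as the number per arm.

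**Step 4. False-positive rate under an assumed offset.** With no true effect and a mean offset of b SD, the test statistic is noncentral t with noncentrality b·√(51/2) = 5.05b. The two-sided critical value at 0.05 is 1.984.

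| Offset b (SD) | Noncentrality | Rejection rate |
|---|---|---|
| 0 | 0 | 5.0% |
| 0.1 | 0.505 | 7.9% |
| 0.2 | 1.010 | 17.0% |
| 0.3 | 1.515 | 32.3% |
| 0.5 | 2.525 | 70.6% |

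The same calculation in clinical units depends heavily on the assumed SD:

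- Systolic pressure, 3 mmHg offset: 46.6%, 32.3%, 24.0% and 17.0% at SD 8, 10, 12 and 15.
- Systolic pressure, 5 mmHg offset: 87.8%, 70.6%, 54.9% and 38.5% at the same SDs.
- SpO2, 1-point offset: 99.9%, 91.5% and 70.6% at SD 1, 1.5 and 2.

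**Step 5. Does the Bonferroni correction in section 2.6 remove it?** The family of tests is not defined, so two cases are shown.

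| Offset b (SD) | α = 0.05/4 = 1.25% (four parameters) | α = 0.05/8 = 0.625% (four parameters, two times) |
|---|---|---|
| 0.2 | 6.7% | 4.1% |
| 0.33 | 20.0% | 14.0% |
| 0.5 | 49.5% | 39.9% |

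The rates fall but stay several times above nominal. The estimate and its confidence interval remain centred on the wrong value whatever α is used.

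**Step 6. What if control-device errors average to zero?** Simulation with 51 per arm and zero-mean device error added in the CG keeps the false-positive rate near 5%. Two-sided power at d = 0.5 falls from about 70% to 66% (device SD 0.5) or 53% (device SD 1.0).

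**The case against.** The strongest reply is that section 2.6 models outcomes at baseline, 6 and 12 months, the same times as the in-person cardiology evaluations in both arms, so clinic readings may be what is meant. The text does not support this. Section 2.5.2 defines the outcomes through the twice-daily home readings and never says that the visits record them, and Table 1 also marks the four parameters between visits.

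Other objections stand and limit the point.

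- A reader might infer that device differences are bound to appear as treatment effects. They need a non-zero average offset. Control devices are of unfixed makes, and their errors may partly cancel.
- A reader might call the control devices uncalibrated or their readings self-selected. The article is silent on checks of control devices. Both arms share the twice-daily schedule, and section 2.3 makes wearable use voluntary, so selective recording is possible in either arm.
- A reader might conclude that inertial sensors are meant to measure blood pressure. The device lists in sections 2.3.2 and 2.4 are worded as examples, and respiratory rate in the CG is recorded manually and need not come from a device. What remains is an unstated source, not an error.
- It would be too absolute to say that nothing could ever separate device from arm. Section 2.2 excludes anyone without access to a home blood pressure monitor and oximeter, so parallel own-device readings in the EG would be possible. Those would be new data; the planned readings alone cannot do it.
- The percentages rest on assumed offsets and SDs and are illustrative only.

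**Conclusion.** The point holds as a matter of design. Device, stated calibration and recording mode of the home readings are all determined by allocation, and any non-zero average offset can be mistaken for a treatment effect. Neither baseline adjustment nor the multiplicity correction removes it. The size cannot be known from the documents. Under the assumptions shown, an offset of 0.2 to 0.3 SD already raises a nominal 5% error to about 17% to 32%, while a zero average offset costs precision only.

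The scope is one group of secondary outcomes; the primary abstinence outcomes are untouched. The change should be made, and section 2.7 states that enrolment has not started.

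**What to change.** In sections 2.5.2 and 2.6:

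1. Define the between-arm cardiopulmonary outcomes as readings taken at the planned in-person cardiology evaluations at baseline, 6 and 12 months, with the same instrument and procedure in both arms, and adjust for baseline.
2. State that these visits record all four parameters.
3. Treat the home readings as within-arm descriptive or adherence data, with no between-arm test.

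As a secondary clarification, state the source of blood pressure in the EG (section 2.3.2) and of respiratory rate in the CG (sections 2.4 and 2.5.2).

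The cost is small but more than wording. The visits exist in both arms, but a common instrument and procedure must be specified and some measurements may have to be added. The between-arm comparison would then rest on three time points instead of a twice-daily series. With a common instrument the average offset is zero by design, and the false-positive rate returns to its nominal level.

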The Wear-Smile project was designed to investigate whether the integration of wearable monitoring technologies and a telemedicine platform into a multimodal smoking cessation pathway may improve abstinence outcomes, treatment adherence, patient engagement, and health-related outcomes compared with standard in-person smoking cessation care. Furthermore, the protocol aims to evaluate the impact of the intervention on cardiovascular, respiratory, oral health, psychological well-being, and quality of life parameters through a multi-specialistic approach.

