### 2.6. Statistical Analysis

An a priori sample size estimation was performed using G*Power software version 3.1.9.7 [36]. The calculation was based on the primary outcome (CAR), assuming a one-tailed test, a type I error (α) of 0.05, a statistical power (1−β) of 0.80, and a medium expected effect size. Based on these assumptions, the estimated sample size is 102 participants (51 per group).

The data collected will be pseudonymized (a technique that modifies and masks personal and sensitive data of a natural person to prevent direct or easy attribution to the individual) and will be used exclusively for the purposes of the Wear-Smile study project.

Statistical analyses will be performed according to the intention-to-treat (ITT) principle. Per-protocol analyses will additionally be conducted as sensitivity analyses.

The statistical analysis will be applied to analyze continuous and categorical variables, with particular attention to the handling of missing data and the analysis of both intra- and inter-subject variability.

To enhance data interpretation and understanding of distributions, graphical representations such as histograms, boxplots conditioned on the target variable, and scatter plots will be employed.

To minimize the risk of bias due to missing data, a missing data analysis will be performed to assess whether data are Missing Completely at Random (MCAR) or dependent on other variables. If missing data exceeds 5%, it will be handled using multiple imputation techniques based on appropriate statistical models, thereby reducing the risk of bias.

The adoption of these methodologies will strengthen the scientific evidence regarding the effectiveness of telerehabilitation for smoking cessation, optimize result interpretation, and provide valuable insights for future clinical implementations and public health policies.

A sensitivity analysis will be conducted to compare results between the original datasets and the imputed datasets.

Statistical analyses will be performed using SPSS version 28.0, R version 4.2, or STATA version 17.0. The level of statistical significance will be set at *p* < 0.05 for all tests, with Bonferroni correction applied for multiple comparisons to control the risk of Type I error. Effect sizes and 95% confidence intervals (95% CI) will also be reported whenever appropriate.

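### The dedicated adherence measures differ by arm in construct and source, and no common measure is named for the between-arm adherence aim

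*Protocol article*

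**What the plan says.** The Introduction (Section 1) asks whether the intervention "may improve abstinence outcomes, treatment adherence, patient engagement, and health-related outcomes compared with standard in-person smoking cessation care". Adherence is therefore a comparative aim. Section 2.5.2 repeats it among the secondary outcomes: "participants’ adherence, usability, acceptability, and patient and healthcare satisfaction with the rehabilitation program".

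The same section sets the timing and names two constructs: "Adherence to the rehabilitation program and compliance with wearable device utilization will be assessed at baseline, 6 months, and 12 months". It then assigns measures by arm:

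- EG: "adherence to wearable device use will be automatically monitored through the telemedicine platform by recording the timing and frequency of device utilization".
- CG: "In the CG, adherence to the rehabilitation program will be evaluated during scheduled in-person follow-up visits". No metric is given.

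Section 2.5.2 also plans the TAAS at 6 and 12 months, alongside a platform-usability scale and a satisfaction questionnaire. It does not limit the TAAS to one arm, but it does not say that the CG completes it.

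On counselling sessions, Section 2.3 states: "All sessions are documented in the electronic health record to ensure traceability, reproducibility, and consistency between the two study arms".

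**The concern.** A between-arm comparison needs the same quantity measured in the same way in both arms. Here the measure assigned to the EG is use of a device, and the measure assigned to the CG is adherence to a programme. One comes from a continuous machine log, the other from an assessment at visits. If the two were set against each other with the tests in Section 2.6, the difference would mix any real difference in adherence with the difference in what was measured and how. At stake is whether the trial can support a statement that telemedicine with wearables improves adherence, which is one of its named aims.

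The baseline assessment is a second, smaller problem. Adherence cannot be observed before there is a programme or a device to adhere to.

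**Working it through.** The plan gives no figure for adherence, so there is nothing to recompute. The sample size of 102 is based on continuous abstinence and has no bearing here. The check sets the sections side by side.

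**1. Construct, source and counterpart**

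| | EG | CG | Where |
|---|---|---|---|
| What is measured | Wearable use | Programme adherence | 2.5.2 |
| How | Automatic platform log | Evaluation at in-person visits, metric not given | 2.5.2 |
| Wearables present | Yes, use is voluntary | None | 2.3, 2.4 |

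The EG log has no equivalent in the CG, and Section 2.5.2 assigns no measure of programme adherence specifically to the EG. The two rows that define the outcome differ by arm.

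**2. What the analysis section adds**

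Section 2.6 lists generic between-arm tests: Student's t or Mann–Whitney for continuous variables, chi-square or Fisher for categorical ones. It names no adherence variable, so it does not settle which measure is compared.

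**3. Measures that could be common to both arms**

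- TAAS: planned at 6 and 12 months and not restricted by arm. It combines acceptability with adherence, and it is a questionnaire rather than observed adherence.
- Session attendance: Section 2.3 places counselling sessions at routine follow-up visits held equally often in the two arms, and documents every session in the health record. Source and denominator are therefore shared.

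Section 2.5.2 designates neither as the comparative adherence outcome.

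**4. Baseline timing**

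- Section 2.1: the allocation envelope is opened only once the baseline assessment is complete and the participant is enrolled.
- Section 2.3: EG training on platform and devices follows enrolment.
- Section 2.5.2: adherence and wearable compliance are nevertheless assessed at baseline.

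At that point no participant has an arm, a device or a programme. Section 2.6 plans mixed models for secondary outcomes over baseline, 6 and 12 months, so adherence would enter them without a meaningful first value. Table 1 does not resolve this: it has rows for usability, acceptability and satisfaction at 6 and 12 months, but none for adherence.

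**The case against.** The strongest reply is that the protocol never says it will compare EG logs with CG visit data. Section 2.5.2 names two constructs and labels the log as adherence to wearable use, not to the programme. The TAAS is planned without restriction by arm. The Discussion (Section 3) also has adherence and device use followed at visits in the context of the intervention group, so EG adherence is not known from logs alone.

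Much of this stands. A reader might infer that the adherence aim cannot be answered at all. The documents do not support that: the TAAS, if given in both arms, and the session records allow a like-for-like comparison. What remains is that the TAAS is not stated outright for the CG, the visit-based monitoring in the Discussion serves to find barriers to engagement and defines no outcome, and the only measures dedicated to adherence are specific to each arm.

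Two further inferences are tempting and also go too far:

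- *Per-protocol selection.* Section 2.6 says "Per-protocol analyses will additionally be conducted as sensitivity analyses", and one might suppose that the set would select EG participants on device use. Nothing ties it to device use, and its definition may properly sit in a fuller document.
- *Dense EG data against a handful of CG visits.* Sections 2.4 and 2.5.2 have CG participants record the same four parameters by hand twice daily for up to 12 months, nominally 2 × 365 = 730 occasions in either arm. The number of counselling visits is not stated.

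**Conclusion.** The point holds in a limited form. Adherence is a between-arm aim, yet its dedicated measures differ by arm in construct and source, so comparing them would confound arm with measurement. A usable common measure exists but is not designated. The baseline adherence assessment has no content, because it precedes allocation and training.

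No numerical bias can be derived from the documents, and none is claimed. The consequence is confined to one secondary outcome; the primary abstinence outcomes under intention to treat are not affected. The conclusion rests on reading Section 2.5.2 as the definition of the adherence outcome and on no other section naming a common measure. It would weaken if the fuller protocol or analysis plan already made the TAAS or session attendance the comparative measure in both arms.

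**What to change.** In Section 2.5.2:

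1. Define the between-arm adherence outcome as the number of scheduled counselling sessions attended divided by the number scheduled, taken from the health record in both arms. Count scheduled sessions only; leave out the on-request teleconsultations (Section 2.3) and the additional in-person evaluations (Section 2.4), since these arise differently by arm.
2. State that the TAAS is completed in both arms at 6 and 12 months, as supporting evidence.
3. Report the wearable-use logs descriptively, for the EG only.
4. Remove the baseline adherence and wearable-compliance assessment, and add an adherence row to Table 1 at 6 and 12 months.

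The cost is a change of wording. The session records are already planned, the TAAS is already planned at these times, and enrolment had not started at submission (Section 2.7). If the TAAS was not meant for the CG, there is the small extra burden of one questionnaire at two visits. The downside is that device use no longer counts as comparative evidence on adherence; it remains available as a description of how the EG used the intervention.
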